## Introduction

Stroke is the first cause of death and disability among adults in China and the second leading cause of death worldwide (Group, 2020). In 2019, among all the subtypes of stroke, ischaemic stroke (IS) had a prevalence of 62.4%, and intracerebral brain hemorrhage (ICH), of 27.9% (GBD 2019 Stroke Collaborators, 2021). Stroke, a life-threatening disease, often leads to severe central nervous system damage in case of untimely treatment (Saver, 2006; Chen et al., 2019). Early neurological deterioration (END) is a frequent and serious complication of acute stroke, with an incidence of 5%–40% (Thanvi et al., 2008; Geng et al., 2017). It is characterized by progressive deterioration of neurological function within 48-72 h after stroke (Celik et al., 2019; Kang et al., 2021). END is strongly associated with an increased risk of functional disability, mortality, and poor 3-month clinical outcomes (Kwan and Hand, 2006; Geng et al., 2017). Currently, vascular recanalization strategies, including intravenous thrombolysis (IVT) and endovascular therapy (EVT), are recommended first-line therapy options for acute ischemic stroke (AIS) (Ma et al., 2019; Powers et al., 2019). However, they only benefit a small number of patients due to narrow time windows, imaging dependence, high risk of bleeding, and limited repass rates (Wang et al., 2019). The treatment options for ICH are also limited (Schrag and Kirshner, 2020). There are no specific drugs for treating ICH, and the benefits and risks of surgical treatment are controversial (Deng and Wu, 2021; Zhang and Zhou, 2022)).

Xingnaojing injection (XNJI) is made using an extract from the An Gong Niu Huang pill, a popular and effective first-aid TCM used for acute stroke, which has been clinically applied for more than 200 years (Deng et al., 2010; Wang, 2022; Wang W. et al., 2022). Using modern pharmaceutical technology, dangerous ingredients, such as cinnabar and realgar, are removed, and four ingredients including musk, gardenia, Yujin, and borneol are retained and refined to obtain a convenient and effective water-soluble intravenous injection (Yue et al., 2019). Many studies have demonstrated the effectiveness and safety of XNJI for acute stroke (Ma et al., 2013; Shen et al., 2020; Wang et al., 2021), and the guidelines and consensus in China have recommended the use of XNJI as stroke first aid (Gao, 2016; Department of Neurology, 2018).

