However, on conducting an overview of systematic reviews and meta-analyses (Tian et al., 2021), we found that none of the included studies reported on the different medication timings of XNJI use in acute stroke and on stroke severity. We also conducted a mixed-methods research (MMR) study (Tian, 2021) and found that early XNJI use within 6 h of stroke onset maybe associated with greater functional improvement. However, the appropriate initiation time of XNJI treatment is also unclear due to medical insurance restrictions and concerns regarding possible incompatibility between XNJI and IVT. A recent systematic review and meta-analysis (Wang L. et al., 2022) have also suggested that the optimum XNJI initiation time during the acute phase might be within the first 72 h after stroke onset, preferably within the first 6 h. However, due to insufficient evidence, it remains unknown whether XNJI should ideally be administered immediately after stroke onset or within 24 h. In addition, in real-world settings, the knowledge and attitude of emergency doctors regarding XNJI used for stroke first aid are also very critical. Therefore, we designed this MMR study to explore the relationship between XNJI used within 24 h of onset and the presence of END 3 days after symptom onset in patients with acute stroke.

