### Inclusion criteria

•Diagnosis of suspected acute stroke•Within 24 h of symptom onset•Age≥18 years

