### Intervention measures

The quantitative research part of this study will be observational. Based on our observation of whether XNJI was intravenously administered within 24 h of onset in the prehospital ambulance setting, patients with acute stroke will be divided into two groups: the exposure group comprising patients who were intravenously administered XNJI and the nonexposure group comprising patients who were not. During the study period, all relevant data will be collected at the following timepoints to facilitate a continuous dynamic observation and evaluation: during the prehospital ambulance service; within 24 h of admission; day 3 after stroke onset; day 10 after stroke onset or the day of discharge; and 30 ± 3, 60 ± 3, and 90 ± 7 days after stroke onset. This research will not interfere with the actual diagnosis and treatment of the participants. The clinicians will make decisions regarding routine treatment options based on the patient’s specific circumstances. The routine stroke treatment will follow the current national guidelines for acute Is and ICH from the Chinese Society of Neurology.

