### Types of outcomes

#### Efficacy outcomes

The primary outcome is END on the third day of onset defined as an increase of 2 or more points in the NIHISS score between baseline and day 3. The secondary outcomes include the rates of stroke-related and any-cause deaths during hospitalization, differences in the changes in the neurological deficit degree, risk grade of ICH evaluated through changes in the ICH scale score from baseline to day 10 or the day of discharge, the proportion of patients with activities of daily living with a Barthel Index score of ≥90, and the proportion of independent patients defined by a modified Rankin Scale score ≤2 at 30 ± 3, 60 ± 3, and 90 ± 7 days after stroke onset. A complete list of the efficacy outcomes analyzed in the TRACE study is presented in Table 2.

**TABLE 2 T2:** | The complete list of efficacy outcomes analyzed in the TRACE study.

Primary outcome
1. Early neurological deterioration# change
Early neurologic deterioration (END) is defined as an increase of 2 points or more in the National Institute of Health Stroke Scale (NIHSS) score between baseline and 3 days. The NIHSS score ranges from 0 (best score) to 42 (worst score). [Time Frame: between baseline and 3 days]
Secondary outcomes
1. Rate of stroke-related deaths and deaths from any cause Rate of stroke-related deaths and deaths from any cause during hospitalization [Time Frame: during hospitalization] 2. Neurological deficit Comparison of the change of degree of neurological deficit evaluated by the NIHSS [Time Frame: baseline and day 10 or the day of discharge] 4. Risk grade of a cerebral hemorrhage Comparison of the change of risk grade of Intracranial hemorrhage evaluated by Intracerebral Haemorrhage (ICH) scale. The ICH score ranges from 0 (best score) to 6 (worst score). [Time Frame: baseline and day 10 or the day of discharge] 5. Activities of daily living Activities of daily living will be measured by Barthel Index (BI) score. The proportion of patients with a BI score of ≥ 90. The BI score ranges from 0 (worst score) to 100 (best score). [Time Frame: 30, 60, and 90 days] 6. The proportion of patients’ independent The proportion of patients’ independence is defined as a modified Rankin Scale (mRS) score of ≤ 2. The mRS score ranges from 0 (best score) to 6 (worst score). [Time Frame: 30, 60, and 90 days]

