Note: Baseline score refers to the NIHISS and ICH scores within 24 h of symptom onset (assessed in a prehospital ambulance or after admission). Abbreviations: TRACE, Trial of a prehospital intervention with traditional Chinese medicine for acute stroke; NIHSS, National Institutes of Health Stroke Scale; ICH, intracerebral hemorrhage; BI, Barthel Index; mRS, modified Rankin Scale.

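### END runs from a baseline NIHSS taken anywhere in the first 24 h to a day fixed from onset, and the unadjusted primary test ignores onset-to-baseline time

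*Protocol article*

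**What the plan says.** **Start of the window.** The note to Table 2 states: "Baseline score refers to the NIHISS and ICH scores within 24 h of symptom onset". It adds that the score may be "assessed in a prehospital ambulance or after admission". The entry criterion has the same width: "Within 24 h of symptom onset". Under Recruitment, onset is taken as the time the patient was last seen well.

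**End of the window.** Efficacy outcomes gives the primary outcome as "END on the third day of onset defined as an increase of 2 or more points in the NIHISS score between baseline and day 3". Intervention measures and Table 1 (Visit 3) count that day from onset: "day 3 after stroke onset". No clock hour is given.

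**When END develops.** The Introduction says of END: "It is characterized by progressive deterioration of neurological function within 48-72 h after stroke".

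**Comparison.** Under Intervention measures, the groups are formed by whether XNJI was observed to be given in the ambulance. Data processing and analysis names Pearson's chi-squared test for the primary comparison, one-sided at 0.05. The only adjustment described is a multivariable linear regression on factors that were significant univariately. Onset-to-baseline time is not named.

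**Times collected.** Table 1 lists times of onset, ambulance arrival and hospital arrival. It lists no time for the NIHSS itself.

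**The concern.** The end of the END window is fixed relative to onset, but its start can move over 24 h. A patient scored soon after onset can show almost the whole course of early deterioration. In a patient scored late in the first day, whatever worsened before the score is part of the baseline and cannot count as END. This holds even if every baseline is a genuine ambulance score.

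In a randomised trial the delay would balance on average. Here exposure follows clinical use, and nothing in the primary analysis corrects an imbalance. If the groups differ in onset-to-baseline time, the primary END comparison partly measures when patients were scored and not what they received. Screening covariates by univariate significance may drop this one, and a linear model does not suit a yes/no outcome.

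**Working it through.** The article gives no figure for this bias. The benchmark is its planned difference (Sample size calculation): 13% − 7% = 6 percentage points.

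**Inputs from the article:** baseline 0-24 h after onset; assessment on day 3 after onset; 13% END without XNJI; one-sided α = 0.05.

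**Assumptions:** day 3 means 72 h; the 13% is the END risk accumulated over 0-72 h; XNJI has no effect; the END hazard is either constant or halves every 24 h; the baseline times are examples.

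**Step 1: window length.** With a baseline at t hours the window is 72 − t: 72 h at t = 0, 60 h at t = 12, 48 h at t = 24.

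**Step 2: END still observable after a baseline at t.**
- Constant hazard: 13% × (72 − t)/72
- Halving hazard, λ = ln2/24: 13% × (e^(−λt) − e^(−72λ))/(1 − e^(−72λ)), where e^(−72λ) = 1/8

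| Baseline | Constant | Halving every 24 h |
|---|---|---|
| 2 h | 13 × 70/72 = 12.64% | 13 × (0.9439 − 0.125)/0.875 = 12.17% |
| 6 h | 13 × 66/72 = 11.92% | 13 × (0.8409 − 0.125)/0.875 = 10.64% |
| 12 h | 13 × 60/72 = 10.83% | 13 × (0.7071 − 0.125)/0.875 = 8.65% |

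Gaps with no drug effect:
- 2 h versus 6 h: 0.7 points (constant) to 1.5 points (halving)
- 2 h versus 12 h: 1.8 points (constant) to 3.5 points (halving)

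**Step 3: effect on the test.** Assume 500 per group and place the 13% at a 2 h baseline. The rate at baseline b is then 1 − exp(−[H(72) − H(b)]), where H is the cumulative hazard. A 12 h baseline gives 11.3% (constant) or 9.4% (halving). The chance of a significant result in favour of XNJI is Φ{[(pc − pe) − 1.645·se0]/se1}, where pc and pe are the unexposed and exposed END rates, se0 is the pooled standard error and se1 the unpooled one. For the constant hazard at 12 h: (0.0175 − 1.645 × 0.0206)/0.0206 ≈ −0.80, or 21%.

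| Timing (no drug effect) | Constant | Halving |
|---|---|---|
| Same mix in both groups | 5% | 5% |
| Exposed 6 h, unexposed 2 h | 9% | 18% |
| Exposed 12 h, unexposed 2 h | 21% | 56% |
| 12 h baseline in 50% of exposed and 20% of unexposed, rest 2 h | 8% | 13% |
| Exposed 2 h, unexposed 12 h | 0.6% | below 0.1% |

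Simulation of the third row agreed (21% and 56%). The last row shows the opposite error: the test is pushed away from XNJI, and a real benefit would be masked.

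**The case against.** **Direction.** A reader might infer that the design produces a false XNJI benefit, because the Introduction mentions "concerns regarding possible incompatibility between XNJI and IVT", which could steer XNJI away from patients reached early. The documents do not support that step. The remark, alongside insurance restrictions, explains why the right starting time is unclear; it does not say that ambulance doctors withhold XNJI from early patients. The same part of the Introduction reports that use within 6 h may be associated with greater improvement and that a review prefers that window. That would favour early use and reverse the bias. This objection stands: the direction is open.

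**Size.** The hazard shapes and delays are assumed, and a whole-group contrast of 2 h against 12 h is strong. The 13% is a day 3 rate from another study, not a known 0-72 h risk, and day 3 has no stated hour. END is also a difference between two scores, so patients may improve after an early baseline, which the hazard model ignores. All of this stands. The figures are illustrations, not estimates.

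**Anchor.** Counting day 3 from onset fits the article's description of END and is not in itself an error. That also stands. The fault is leaving the floating start unaccounted for.

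**Deferral.** A fuller analysis plan may add detail. However, the article itself fixes the baseline window, the onset-based endpoint and the unadjusted primary test, so the point concerns what is stated and not what is left out.

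**Conclusion.** The point holds as a two-directional bias. Patients scored later have a shorter and later END window, and the primary test takes no account of it. If exposed patients are scored later, the error favours XNJI; if they are scored earlier, it hides a benefit; if timing is alike in both groups, it vanishes. The article gives no timing by group, so a claim that the trial will show a spurious benefit goes further than the text allows.

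Under the assumptions in the working, the distortion is 0.7 to 1.5 points for a 4 h difference in baseline time and 1.8 to 3.5 points for a 10 h difference, against a planned 6. The lower figures are modest. The highest is more than half the planned effect, but needs both a large timing gap and a falling hazard. The shorter window itself follows from the definitions alone. A correction is worthwhile because it is cheap and protects the primary result in either direction.

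**What to change.** - Make the primary END comparison either stratified by onset-to-baseline time (for example 0-3, >3-6, >6-12 and >12-24 h) or adjusted for it in a binary model such as logistic regression. Enter the time as a forced covariate, not one selected by univariate significance.
- Report the distribution of onset-to-baseline time by group.
- Compute it from the recorded onset time together with ambulance-arrival time for prehospital baselines, or hospital-arrival time for post-admission baselines. State for each patient which score served as baseline, since that decides the proxy.

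**Cost.** This is mainly analysis wording, with a small loss of precision. Because Table 1 lists no NIHSS clock time, the proxy carries some error, likely larger for post-admission baselines.

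**Not recommended:** moving the END assessment to 72 h after baseline. This equalises the window's length but not its later start. Under the halving hazard the observable risk becomes 13% × e^(−λt): 12.27% at 2 h and 9.19% at 12 h, still a 3.1-point gap against 3.5. It would also place scores up to 24 + 72 = 96 h after onset and change the primary outcome late in a recruitment period running from March 2018 to an estimated end in December 2022.

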#### Safety outcomes

We defined an AE as any unfavorable and unintended sign, symptom, or disease that develops in the participants in both groups during the trial period regardless of whether or not it is related to the XNJI treatment (Lai et al., 2017). Safety outcomes will be assessed by routine physical and laboratory examinations and AEs recording during the observation period. Because the methodology of the study does not interfere with the actual clinical diagnosis and treatment, we changed our approach from AEs processing to AEs recording. If AEs occur during hospitalization, it will not need to be reported; however, relevant information (start time; symptoms/signs; intensity; attack frequency, duration, and termination time; laboratory indicators; treatment methods and outcomes; follow-up results; etc.) will have to be accurately recorded. The use of all concomitant medications should be recorded in detail. If any treatment is required, a record should be made regarding the treatment administered.

### Quality control and monitoring

Before registration, several approaches will be implemented to ensure coordination among the different centers to avoid the potential heterogeneity of data. First, all the research personnel at each center and independent interviewers will be trained so that they understand the clinical trial protocol and comply with the SOP for consecutive patient screening and recruitment, obtaining informed consent, and collecting data (scale filling, scale evaluation, eCRF filling), etc; this will be achieved through centralized on-site training, videoconferences, and training videos. Second, special quality auditors will be set up in each subcenter and will conduct regular in-institution quality audits, which will include the subject registration process, the implementation of registration standards, data authenticity and traceability, data collection integrity, etc. Third, an independent and professional third-party supervision agency will perform the main supervision task of the research group. The monitoring personnel will set up the monitoring task, frequency, and time points according to the research risks; they will regularly analyze and deal with the research risks under the guidance or approval of the group leadership unit. The data monitoring process is divided into two parts: on-site monitoring and remote network center monitoring. Remote monitoring will be carried out based on the project management platform and EDC system. In this study, the data quality monitoring will mainly be conducted remotely, and standardization, compliance, and data authenticity monitoring during the research process will mainly be conducted on-site. The supervisor will contact the research assistants, researchers, and central quality control personnel from time to time to ensure the implementation of the research and quality control process. A clinical research associate (equivalent to a clinical study monitor, CRA) will visit the research centers regularly or irregularly for site inspection. The CRA will be responsible for tasks such as the following: to check whether the documents recorded are timely, complete, accurate, and true; to check whether the signing of the informed consent form complies with good clinical practice (GCP) and relevant regulatory requirements; to ensure that all the data collected via the eCRF are consistent with the original data, such as those in the hospitalization medical records; and to ensure that all AEs are recorded.

### Sample size calculation

According to the definition of the dominant population, at least one particular subgroup will have a positive outcome in terms of the primary efficacy index. A previous study conducted in Germany reported that approximately 13% of patients exhibited END on the third day after stroke onset (an increase of 2 or more points in the NIHSS score). Data obtained from our previous research as well as other domestic research showed that the rate of END on the third day after stroke onset was approximately 6–8%. The sample size was calculated on the following assumptions: the END rate in patients who did not receive the TCM intervention was 13% based on data from studies conducted overseas, and the END rate in patients who received the TCM intervention was 7% based on domestic data. Since there is no formula meant specifically for calculating the sample size in registry studies, we decided to use the one-sided difference test based on the statistical analysis method and formula for calculating the sample size in cohort studies. Consequently, the following formula, where α = 0.05 and β = 0.2, was used:
$$\text{n}={\left[\frac{Z_{1}-\alpha \sqrt{2\text{pq}}+Z_{1}-\beta \sqrt{{\text{p}}_{1}\left(1-{\text{p}}_{1}\right)+{\text{p}}_{2}\left(1-{\text{p}}_{2}\right)}}{{\text{p}}_{1}{-\text{p}}_{2}}\right]}^{2}.$$

The smallest sample size for a single cohort was estimated to be 426 patients; therefore, a minimum of 852 patients must be included. Considering the uneven distribution of exposure factors among patients and the inability of some patients to attend all the visits through the 90 days, the sample size was increased to 1,000 cases, which is an increase of 17% on the original base size.

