### Recruitment

Patients will be recruited consecutively from 20 participating sites, including both Western medicine hospitals and TCM hospitals in Beijing, China, which have the capability of conducting qualified research and express a proven commitment to the study. The recruitment started in March 2018 and is estimated to end in December 2022. Eligible adult patients with suspected acute stroke within 24 h of onset will be sent to the hospital by ambulance. We plan to recruit 1,000 patients with confirmed acute stroke based on the inclusion and rejection criteria. The time of stroke onset was defined as the time at which the patient was last observed to be well. Only those who meet the inclusion criteria and willingly provide written informed consent will be recruited. Since this is an observational study that involves a specific prehospital emergency intervention, it is difficult to obtain written informed consent from the patient in the prehospital ambulance setting. The patient will be asked to sign a written informed consent form in the hospital. The researchers will inform patients of the benefits and risks of participating in the research and of the need to analyze their prehospital information in addition to their in-hospital information; they will also be assured that this will not interfere with the actual clinical diagnosis and treatment. Legal guardians will sign the informed consent form on behalf of patients in a coma. If the patient or his legal guardian does not agree to the use of the diagnosis and treatment-related information in this study, the prehospital information will not be used. The participation of patients will be entirely voluntary, and their data will be strictly protected to the extent permitted by the law.

In this study, to increase the rate of identifying suspected stroke patients, the prehospital assessment scale for identifying these patients was changed from the Face-Arms-Speech-Time (FAST) scale to the Balance-Eyes-Face-Arms-Speech-Time (BEFAST) scale. Once meeting the inclusion criteria, patients will be included and registered immediately in an ambulance. However, due to the busy task and high tension in the prehospital ambulance setting, ambulance doctors are unable to exclude patients in detail. The ineligible patients will be rejected after admission. Therefore, this study has changed the exclusion criterion to the rejection criterion. 

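### The planned END effect (13% vs 7%) sets a German rate against a domestic one, so it mixes country with treatment; on domestic control rates of 6–8% the power may fall short of the stated 80%

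*Protocol article*

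**What the plan says.** The section Sample size calculation in the protocol article gives two background rates for END on day 3, defined as a rise of at least 2 NIHSS points. The first is foreign: "A previous study conducted in Germany reported that approximately 13% of patients exhibited END on the third day after stroke onset". The second is Chinese: "other domestic research showed that the rate of END on the third day after stroke onset was approximately 6–8" per cent. Neither is described by XNJI exposure.

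The section then assigns one rate to each cohort. For the nonexposed, "the END rate in patients who did not receive the TCM intervention was 13% based on data from studies conducted overseas". For the exposed, "the END rate in patients who received the TCM intervention was 7% based on domestic data". The test is one-sided ("we decided to use the one-sided difference test") with "α = 0.05 and β = 0.2", that is, 80% power. The result is given as 426 per cohort, 852 in all, raised to 1,000 to allow for uneven exposure and missed visits. No exposure ratio or loss rate is stated.

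On the setting, Recruitment says: "Patients will be recruited consecutively from 20 participating sites, including both Western medicine hospitals and TCM hospitals in Beijing, China". Exposed and nonexposed patients thus come from the same city and the same sites.

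**The concern.** A planning effect should estimate what differs between the two cohorts of this study. Here one rate is German and the other Chinese, and the section offers no comparison of exposed with unexposed patients within one population. Any difference between the countries in stroke type, severity, time of first assessment or routine care enters the 6-point effect as if XNJI had caused it.

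The rate on paper closest to Beijing patients is the domestic one, yet it is used only for the exposed. If the nonexposed rate is nearer to that figure than to 13%, there are fewer events than planned, and the same relative effect is a smaller absolute difference. The stated 80% power may then not hold, and readers could take a non-significant result as stronger evidence against an effect than it is.

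**Working it through.** **Inputs.** From Sample size calculation: 13% and 7%, domestic range 6–8%, one-sided α = 0.05, β = 0.2, 426 per cohort, 1,000 in total. Assumed here, because the article gives no within-population effect: the planned relative risk 7/13 = 0.538, or alternatively the planned odds ratio (0.07/0.93)/(0.13/0.87) = 0.504.

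**Step 1: the plan's own figure.** The printed formula is n = {[z(1−α)·√(2pq) + z(1−β)·√(p1q1 + p2q2)] / (p1 − p2)}², where p is the mean of the two rates, here 0.10.

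- First term: 1.645 × √0.18 = 0.698.
- Second term: 0.842 × √(0.1131 + 0.0651) = 0.355.
- n = (1.053/0.06)² = 308.1, so 309 per cohort.

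The stated 426 is not reproduced. With β = 0.1 the second term is 1.282 × 0.422 = 0.541 and n = (1.239/0.06)² = 426.3. A two-sided calculation with continuity correction gives 424, which is also close. This mismatch is a separate matter. It means that 426 per group would have 90% power for 13% vs 7%, and 500 per group 94%. The benchmark used below is the 80% that the article states.

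**Step 2: power with a domestic control rate.** Power = Φ{[|p1 − p2| − 1.645·√(pq(1/n1 + 1/n2))] / √(p1q1/n1 + p2q2/n2)}, with p the pooled rate weighted by group size.

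Example, 7% vs 7% × 0.538 = 3.77%: the difference is 0.0323 and the pooled rate 0.0538.
- At 426 per group: (0.0323 − 1.645 × 0.01547)/0.01543 = 0.445, so power is 67%.
- At 500 per group: (0.0323 − 1.645 × 0.01428)/0.01424 = 0.620, so power is 73%.

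Relative risk 0.538 kept, one-sided 5%. The 700:300 nonexposed:exposed split is my assumption:

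| Nonexposed | Exposed | 426:426 | 500:500 | 700:300 |
|---|---|---|---|---|
| 6% | 3.2% | 61% | 67% | 57% |
| 7% | 3.8% | 67% | 73% | 64% |
| 8% | 4.3% | 73% | 78% | 70% |
| 10% | 5.4% | 81% | 86% | 80% |

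With the odds ratio 0.504 kept, control rates of 6%, 7% and 8% give 65%, 70% and 75% at 426 per group, and 71%, 76% and 81% at 500 per group.

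**Step 3: if the domestic source was partly treated.** Suppose a share f of the patients behind a domestic 7% received XNJI and the relative risk is 0.538. The untreated rate is then 7%/(1 − f + 0.538f).
- f = 0.5: 7%/0.769 = 9.1%. Power is 78% at 426 per group and 83% at 500.
- f = 0.7: 7%/0.677 = 10.3%. Power is 82% and 87%.

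**Step 4: smallest detectable effect.** This is the exposed rate that gives 80% one-sided power with 1,000 complete patients:

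| Nonexposed | 500:500 | 700:300 |
|---|---|---|
| 6% | 2.8% | 2.5% |
| 7% | 3.5% | 3.2% |
| 8% | 4.2% | 3.9% |
| 10% | 5.8% | 5.4% |

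**The case against.** A reader might infer that nonexposed Beijing patients must have an END rate of 6–8%, so that the study is shown to be underpowered. The documents do not support that. The treatment status of the domestic data is not given. Part of it is the authors' own earlier research, the Introduction mentions an earlier study of theirs on the timing of XNJI, and the abstract describes XNJI as in wide use. The domestic rate may come from treated, untreated or mixed patients, and Step 3 shows that a mixed source removes much or all of the shortfall. Had all of those patients been treated, 7% would be a fair exposed rate, though the 13% would still be foreign.

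Nor can 13% be called impossible. The Introduction gives an END incidence of 5%–40%, and this cohort is brought in by ambulance and combines ischemic stroke with hemorrhage. The figure is poorly supported, not ruled out.

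Two further cautions stand. The relative risk carried forward in Step 2 comes from the very contrast under criticism, so those powers are scenarios. And sensitivity to only about a halving of END is no new weakness, since the planned relative risk of 0.54 was already close to that.

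What remains untouched is that the effect comes from two countries, while both cohorts come from one city, and the article gives nothing to separate treatment from setting.

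**Conclusion.** The point holds in conditional form. The planned contrast is confounded with country and case mix, and 13% has no support as the nonexposed rate in Beijing. The size of the consequence depends on facts that the article does not give:

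- Control rate 6–8% and relative risk 0.54: power is 61–73% at 852 patients and 67–78% at 1,000, so 2 to 13 points below the stated 80% at the full size.
- Same control rates and odds ratio 0.50: 65–75% and 71–81%, so 80% is reached only at the top of the range.
- Untreated rate of about 9–10%, from a partly treated domestic source: 78–87%, so little or no shortfall.

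All three assume equal groups, and the figures for 1,000 also assume no loss. The increase from 852 to 1,000 was meant to absorb imbalance and missed visits, so 500 complete patients per group is the best case. At an assumed 700:300 split, power for 7% vs 3.8% is about 64%.

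**What to change.** Keep 1,000 patients and rewrite the sample size paragraph:

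- State whether the patients behind the domestic 6–8% received XNJI, and in what proportion.
- Replace the single overseas control rate with a domestic-based range: 6–8%, extended to about 10% if the source was partly treated.
- Over that range, give the power for a stated relative effect and the smallest detectable difference, one-sided as planned, for the expected exposure split and loss. Mark 7% vs 3.5% at 500:500 as the best case.
- Commit to reporting the 95% confidence interval of the END risk difference, and say that a non-significant result does not exclude effects smaller than the detectable one.

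The cost is one paragraph of rewording, a check of the domestic sources and probably a less favorable stated power. No patients are added, and neither the primary outcome nor the primary test changes.
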